## Abstract

**Background:**

Rural African people living with HIV face significant challenges in entering and remaining in HIV care. In rural Uganda, for example, there is a threefold higher prevalence of HIV compared to the national average and lower engagement throughout the HIV continuum of care. There is an urgent need for appropriate interventions to improve entry and retention in HIV care for rural Ugandans with HIV. Though many adults living with HIV in rural areas prioritize seeking care services from traditional healers over formal clinical services, healers have not been integrated into HIV care programs. The Omuyambi trial is investigating the effectiveness of psychosocial support delivered by traditional healers as an adjunct to standard HIV care versus standard clinic-based HIV care alone. Additionally, we are evaluating the implementation process and outcomes, following the Consolidated Framework for Implementation Research.

**Methods:**

This cluster randomized hybrid type 1 effectiveness-implementation trial will be conducted among 44 traditional healers in two districts of southwestern Uganda. Healers were randomized 1:1 into study arms, where healers in the intervention arm will provide 12 months of psychosocial support to adults with unsuppressed HIV viral loads receiving care at their practices. A total of 650 adults with unsuppressed HIV viral loads will be recruited from healer clusters in the Mbarara and Rwampara districts. The primary study outcome is HIV viral load measured at 12 months after enrollment, which will be analyzed by intention-to-treat. Secondary clinical outcome measures include (re)initiation of HIV care, antiretroviral therapy adherence, and retention in care. The implementation outcomes of adoption, fidelity, appropriateness, and acceptability will be evaluated through key informant interviews and structured surveys at baseline, 3, 9, 12, and 24 months. Sustainability will be measured through HIV viral load measurements at 24 months following enrollment.

**Discussion:**

The Omuyambi trial is evaluating an approach that could improve HIV outcomes by incorporating previously overlooked community lay supporters into the HIV cascade of care. These findings could provide effectiveness and implementation evidence to guide the development of policies and programs aimed at improving HIV outcomes in rural Uganda and other countries where healers play an essential role in community health.

**Trial registration:**

ClinicalTrials.gov NCT05943548. Registered on July 5, 2023. The current protocol version is 4.0 (September 29, 2023).

**Supplementary Information:**

The online version contains supplementary material available at 10.1186/s13063-024-08286-4.

## Background

In Uganda—as in most African countries—the majority of the population resides in rural communities [1]. Rural areas bear a disproportionate burden of HIV; in Uganda, there is a nearly threefold increase in the prevalence of HIV in some rural areas compared to the national level [2]. According to the most recent Ugandan population-based HIV impact assessment, only 66% of rural people living with HIV (PLWH) are aware of their status, compared to 86% of urban PLWH. Furthermore, only 39% of rural PLWH are on antiretroviral therapy (ART), and 23% are virally suppressed, compared to 75% and 59% of urban PLWH, respectively [3]. Overall, rural populations demonstrate 15–25% lower engagement in the HIV continuum than their urban counterparts [4]. These data indicate a pressing need for appropriate and effective strategies to improve rural HIV care to achieve the UNAIDS 95–95-95 benchmarks [5].

In rural areas, PLWH encounter many challenges accessing and consistently engaging in HIV care. Clinics are few and far between, often necessitating expensive motorized transportation. Consequently, regular clinic visits are challenging for individuals living in poverty [6–8]. Moreover, a considerable number of rural PLWH harbor mistrust toward medical care, stemming from fears of stigma associated with being spotted at an HIV clinic, concerns over breaches in confidentiality, and perceived mistreatment from clinicians [9–12]. A lack of social support and diminished self-efficacy among these populations further contribute to disinterest and disengagement from HIV care [13, 14]. Therefore, community-based strategies designed to overcome these obstacles will likely be particularly beneficial for rural PLWH.

Decentralized HIV care mitigates barriers for rural populations by shifting support mechanisms to communities where PLWH reside. The strategy of training community lay providers to offer nonclinical support, such as psychosocial guidance and adherence support, has effectively increased entry and retention in the HIV continuum of care throughout HIV-endemic global settings [15–20]. Consequently, decentralized care has been recognized and integrated into AIDS control strategies by major health organizations, including the World Health Organization (WHO), the Ugandan Ministry of Health, and the President’s Emergency Plan for AIDS Relief (PEPFAR) [17, 21, 22]. Existing community-based programs, however, primarily involve community health workers, village health teams, and peers of PLWH. Traditional healers (TH) largely remain untapped resources as community lay supporters. This fact is a particularly relevant oversight given that > 80% of African populations routinely use TH—both as an adjunct to, or instead of, formal biomedical care. TH are often the first point of contact for healthcare services in their communities, and many adults, including PLWH, may preferentially visit TH because of their accessibility and ubiquity in the region [23, 24]. Therefore, leveraging TH to provide HIV support to their clients provides a potential opportunity to improve HIV outcomes in rural communities [9, 25–27].

The Omuyambi trial aims to evaluate the effectiveness of TH-delivered nonclinical support for adults with unsuppressed HIV viral loads in rural Uganda. This trial adopts an implementation science approach to evaluate contextual determinants, facilitators, and barriers to implementing this novel program. Our central hypothesis is that training TH to engage and support rural PLWH will improve HIV viral load suppression compared with standard care. This study has two objectives:Determine the effectiveness of TH-delivered support (intervention) on HIV viral suppression versus standard clinic-based HIV care alone (control) in a cluster randomized trial. Secondary clinical outcomes include (re)initiation of HIV care, ART adherence, and retention in care.Evaluate the context, facilitators, and barriers pertaining to the implementation of the TH-delivered program. This evaluation will be guided by the Consolidated Framework for Implementation Research (CFIR) domains of intervention characteristics, individuals involved, inner setting, outer setting, and implementation process [28–31]. Implementation outcomes will include adoption, acceptability, appropriateness, fidelity, and sustainability.

### Evidence-based program selection and adaptation

Prior to study initiation, the Omuyambi study team identified an evidence-based lay counseling program that could be adapted for TH delivery. We selected the Patient Advocate Program to adapt to rural Ugandan healers. This community health worker-delivered intervention was developed for PLWH who defaulted from care and assists in (re)linking PLWH to HIV care, supporting ART (re)initiation and adherence through medication counseling, and facilitating retention in care through the provision of individual psychosocial support. A multicenter cohort study among ~ 67,000 PLWH at 57 sites in South Africa showed that the Patient Advocate Program improved viral suppression 8 years after ART initiation compared with routine care (88.6 vs. 80.6%, adjusted RR = 1.53) [32, 33]. This evidence-based program required adaptation for our setting, as it was developed in a semiurban South African context with a robust force of community health workers, unlike rural Uganda. We adapted the program for TH as they are accessible and trusted lay providers in rural Ugandan communities where health facilities are scarcer, literacy is lower, and baseline viral suppression is poorer than the original intervention location. Details of the adaptation process and pilot testing of the TH-delivered program can be found in Sundararajan et al. [34].

## Methods

### Study design

This is a hybrid type I effectiveness-implementation study, where the effectiveness of an intervention is evaluated while concurrently collecting data on program implementation. This effectiveness study is a parallel-arm, cluster randomized trial that will assess the impact of TH-delivered psychosocial support as an adjunct to standard care (intervention) versus standard HIV clinic-based care alone (control) on HIV viral load. The unit of randomization in this study is the individual TH. TH randomized to the intervention arm will provide psychosocial support to PLWH with unsuppressed HIV viral loads who receive traditional care at their practices. Intervention effectiveness will be measured through the primary outcome of HIV viral load suppression at 12 months after enrollment, with secondary clinical outcomes that include (re)initiation in HIV care, ART adherence, and retention in care. Implementation will be evaluated via in-depth interviews and structured surveys among key stakeholders (TH, PLWH, clinicians, and health officials from the Ministry of Health AIDS Control Division Officers and District Health Offices). Implementation barriers and facilitators will be identified, in addition to outcomes such as intervention adoption, fidelity, acceptability, appropriateness, and sustainment. The Omuyambi clinical trial flowchart (Fig. 1) provides a summary of the study design and outcomes. The SPIRIT checklist was used to guide protocol development (Additional File 1) [35].

**Fig. 1 Fig1:**
[figure not shown]
Omuyambi clinical trial flowchart

### Study setting

This trial will be conducted in two rural districts of southwestern Uganda (Mbarara and Rwampara). These study regions are ~ 250 km from the capital, with a population of 480,000 across 1780 km^2^ [36]. The prevalence of HIV is 8% in the Mbarara and Rwampara districts, exceeding the national prevalence of 6% [3]. HIV care in the study region is provided at no cost in 15 government-run hospitals and health centers. Five government HIV clinics within the study region were selected to serve as referral sites for the study. These represent the five clinics where most of the PLWH in our prior studies in the region received care. Forty-four eligible TH were identified and then randomized to cluster sites (please see the “Study population and eligibility criteria” and “Randomization” sections below for details). PLWH will be recruited from these TH clusters. Figure 2 depicts a geographical map of the 5 designated HIV referral clinics and 44 enrolled TH locations. For implementation evaluations, clinicians will be recruited from referral HIV clinics, and health officials will be recruited from the Ministry of Health and District Health offices.

**Fig. 2 Fig2:**
[figure not shown]
Geographical map of the 5 designated HIV referral clinics and 44 enrolled TH locations

### Study population and eligibility criteria

#### Inclusion criteria

##### For PLWH

Positive point-of-care HIV Oraquick Test result or CASE Adherence Index Questionnaire [37] score ≤ 10HIV viral load ≥ 200 copies/mL [38] at the time of enrollmentAge ≥ 18 yearsPrimary residence in Mbarara or Rwampara districtsSelf-reports of not being in clinical care if previously diagnosed with HIVAble to provide informed consent

##### For traditional healers

Monthly volume of ≥ 5 adult clientsLocation ≥ 3 km from another participating TH clusterAge between 18 and 75 years, inclusiveAgreements to attend all training/courses associated with their respective study armsAble to provide informed consent

##### For HIV clinicians and officers from the Ministry of Health AIDS Control Division or District Health Office

Being employed in their position for ≥ 1 yearAged 18 or olderAble to provide informed consentPatient-facing roles (physician, nurse, social worker, counselor) in one of the referral clinics

Potential participants who do not meet the inclusion criteria are ineligible. There are no specific exclusions.

### Interventions

#### Procedures for both study arms

Prior to trial initiation, all 44 TH will participate in a day-long training led by HIV clinicians, which will include information on HIV transmission and prevention, pre- and post-HIV test counseling, and the use of oral swab self-testing kits. The training curriculum is shown in Table 1. Refresher training will take place at 6-month intervals after the initial training to reinforce these concepts and facilitate discussions between TH and clinicians.

**Table 1 Tab1:** Omuyambi training curriculum

**Day 1 (both study arms)**
1. HIV/AIDS overview
a. Knowledge and epidemiology of HIV in Uganda
b. Rationale for ART use and adherence (U = U)
2. Ethics of working with PLWH
a. Confidentiality and status disclosure
b. Discrimination and stigma
3. Overview of clinical services for PLWH
a. Enrollment and pre-ART counseling
b. ART initiation
c. Treatment of other opportunistic infections
d. Adherence support and monitoring
4. Overview of study procedures
a. HIV pre- and post-test counseling
b. Use and interpretation of Oraquick HIV self-testing
c. Linking newly diagnosed patients to HIV care
**Day 2 (intervention only)**
1. Community resources for PLWH
a. NGO or government offices
b. Community support groups
c. Advocacy groups for stigma reduction
2. ART readiness, adherence barriers/facilitators
3. The role of lay adherence supporters
a. Supporting PLWH outside the clinic
b. Lay support versus clinical care roles
c. Lay supporter as advocate and confidante
4. ART adherence support strategies
a. Strengths-based counseling/self-efficacy
b. Managing ART side effects
c. Emphasizing goals of treatment
5. Communication skills for psychosocial counseling
**Day 3 (intervention only)**
1. Strategies for healthy/positive living
a. Nutrition, exercise, and mental health
b. Routine healthcare and clinic visit
c. Safer sex
2. HIV status disclosure and social support
a. Counseling on disclosure strategies
b. Improving social support
3. Identifying mental health symptoms
a. Introduction to depression and anxiety
b. Common symptoms and solutions
c. When to refer PLWH for further management

Our team previously demonstrated the feasibility and effectiveness of TH-facilitated rapid HIV testing [39]. As such, both intervention and control healers will identify new PLWH at their practices through oral-swab HIV self-testing kits (OraQuick ©). To be eligible to receive a self-testing kit, clients must be ≥ 18 years or older, report no prior HIV diagnosis, and have not had an HIV test in the past 12 months. TH in both study arms will also use the CASE adherence index to screen for disengagement from care and ART nonadherence among known PLWH [37]. Potentially eligible clients (newly diagnosed or with CASE adherence scores ≤ 10) will be consented by a study team member, and a venous blood sample will be collected to confirm study eligibility via an HIV viral load assay.

Eligible PLWH in both study arms will be referred to one of five government-run HIV clinics where they can receive free HIV care according to Ugandan MoH guidelines [17]. One clinician from each of the five referral clinics will serve as a clinical liaison and will be responsible for helping to arrange linkage to care appointments and tracking clinic attendance among PLWH participants. TH and PLWH participants will cooperatively select which of the five referral clinics best suits their needs. As the cost of transport to clinic appointments is a known barrier to accessing HIV care, all PLWH will be provided with funds to cover the cost of transportation to their first clinic appointment [40, 41].

#### Control arm study procedures

No additional linkage or psychosocial support will be delivered at the control arm cluster sites to PLWH other than the compensation provided for transportation to (re)establish HIV care. The control arm TH will receive monthly compensation for the time spent facilitating HIV self-testing, referring clients with reactive tests, and identifying PLWH who have defaulted from care. Additional phone voucher reimbursements will be provided to facilitate communication with the study team.

#### Intervention arm study procedures

The TH clusters randomized to the intervention arm will attend two additional days of training prior to the launch of the trial. These training sessions will focus on the principles and strategies for delivering psychosocial support to PLWH. For enrolled PLWH, intervention TH will actively facilitate linkage to one of the five predetermined referral clinics, with the goal of rapid linkage to care within 7 days, according to World Health Organization guidelines [42–44]. The PLWH have the option for the TH to accompany him/her to clinical appointments.

Over the following 12 months, TH will provide psychosocial support for PLWH via the TH-tailored curriculum as an adjunct to routine HIV care. TH will employ one-on-one counseling to improve self-efficacy, provide social support, and develop individualized adherence strategies for participating PLWH. Psychosocial support will be delivered through approximately 30-min meetings with the PLWH. TH will meet with PLWH weekly for 1 month. After that, meetings occur once a month unless TH determine a need for more frequent meetings. TH and PLWH can schedule phone calls when in-person meetings are not possible. TH will be encouraged to use a pragmatic approach to incorporate core elements of the intervention and tailor these components for individual PLWH. There will be no charges to clients for recurring TH visits associated with Omuyambi. The intervention TH will receive a monthly stipend as compensation for work as lay supporters, plus reimbursement in phone vouchers to facilitate communication with RAs, PLWH, and clinical liaisons.

### Trial outcomes

All trial outcomes are summarized in Table 2.

**Table 2 Tab2:** Omuyambi trial outcomes

Domain	Measurement	Method of measurement	Outcome definition	Time point
**Primary clinical outcome**	HIV-1 RNA viral load in blood plasma samples	Abbott HIV-1 assay of venous blood sample	Plasma HIV-1 RNA < 200 copies/mL^2^	12 months following enrollment
**Secondary clinical outcomes**				
Rapid linkage to HIV care	PLWH attending a clinic visit within 7 days of study enrollment	Clinical liaison or HIV treatment card documentation	Completing first clinic visit within 7 days of enrollment	7 days following enrollment
Adherence to ART	Tenofovir concentration in hair samples	Hair sample analysis	Hair tenofovir concentration of > 0.023 ng/mg	12 months following enrollment
Retention in HIV care	PLWH attending most recent HIV clinical appointment	Clinical liaison or HIV treatment card documentation	Attending the most recent appointment within 90 days of its scheduled date	12 months following enrollment
**Implementation outcomes**				
Adoption	The proportion and representativeness of intervention agents who are willing to initiate a program	TH who agree to participate of the total number invited	Proportion of TH who participate compared with those eligible	Baseline
Acceptability	Theoretical Framework of Acceptability (TFA) scale and qualitative interviews	Structured survey and qualitative interviews with PLWH, TH, and clinicians	Perceived complexity and relative advantage of the intervention	Baseline, 12, and 24 months after study initiation
Appropriateness	Qualitative interviews	Interviews with PLWH, TH, and HIV clinicians	Perceived fit, relevance, and compatibility of the intervention for the study setting	Baseline, 12, and 24 months after study initiation
Fidelity	Observation checklist	Structured observations of intervention TH	Degree to which the intervention was implemented consistently across settings	Quarterly
Sustainment	HIV-1 RNA viral load in blood plasma samples	Abbott HIV-1 assay of venous blood sample	Sustained impact of intervention on HIV continuum of care	24 months after study initiation

#### Effectiveness outcomes

The primary study outcome is HIV viral suppression (serum viral load < 200 copies/mL) among PLWH at 12 months following study enrollment. Plasma samples will be processed to obtain HIV-1 RNA viral load concentrations at the Epicenter Mbarara Research Base using the Abbott HIV-1 assay. This test is > 90% sensitive and specific [45–47]. The secondary outcomes will be (1) (re)linkage to care within 7 days; (2) ART (re)initiation; (3) ART adherence at 12 months after linkage to care, defined as a binary outcome of hair tenofovir concentration (> 0.023 ng/mg, reflecting four or more ART doses per week); and (4) retention in HIV clinic care after 12 months [48, 49].

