### Sample size

Study power calculations are based on the primary hypothesis that the intervention will improve viral suppression by 20% using standardized methods for cluster randomized trials [51]. Based on population-level data from the Ugandan Ministry of Health, we assume that the proportion of PLWH achieving the primary outcome of viral suppression will be 60% in the control arm versus 80% in the intervention arm [3]. The results of prior community-based and psychosocial HIV support interventions were used to inform this estimated effect size [32, 52, 53]. To ensure 85% power to detect a difference of ≥ 20% in viral suppression between arms and assuming a 10% loss-to-follow-up rate, we will enroll a minimum of 16 PLWH in each cluster. The target sample size is 650 PLWH, with 325 PLWH in each arm. Forty-four TH will be enrolled as cluster sites, with 22 in each study arm.

As part of the implementation evaluation, we will purposively recruit 20 PLWH, 20 HIV clinicians, and 7 policymakers for participation. The sample size of 20 HIV clinicians is based on prior research showing that thematic and conceptual data saturation is obtained after 12–16 interviews have been conducted within a subgroup [54, 55]. Due to the limited number of policymakers, 7 interviews will be conducted to understand local and national government priorities and implementation context.

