### Participant timeline

Please see Table 3 for the detailed schedules of activities for each participant group.

**Table 3 Tab3:** Detailed schedules of activities for each participant group

People Living with HIV (PLWH) Schedule of Activities							
**Period/Phase**	**Screening/Baseline**	**Day 15**	**Day 29**^**d**^	**Day 43**^**d**^	**Day 57**^**d**^	**12-Month F/u**	**24-Month F/u**
**Study Day**	**D1**	**D15**	**D29**	**D43**	**D57**	**D365**	**D731**
**Study Week**	**W1**	**W2**	**W4**	**W6**	**W8**	**W52**	**W104**
**Study Visit**	**1**	**2**	**3**	**4**	**5**	**6**	**7**
**Window (Days)**		** ± 7**	** ± 7**	** ± 7**	** ± 7**	** + 30**	** + 30**
Oraquick HIV Testing^a^	x						
Case Adherence Index Questionnaire^b^	x						
Informed Consent	x						
Assessment of Inclusion/Exclusion Criteria	x						
Demographic Collection^c^	x						
Medical History	x						
HIV History	x						
FSSQ [56]	x					x	x
HIV-ASES [57]	x					x	x
HIV Stigma Questionnaire [58]	x					x	x
HIV-SMS [59]	x					x	x
HIV-KQ-18 [60]	x					x	x
Quality of Life (MOS-HIV) [61]	x					x	x
TFA [62]	x					x	x
Dried Blood Sampling						x	x
Hair Sample Collection						x	
Patient Enrollment card	x					x	x
**Interviews (will be conducted for specified patients)**	x					x	x
*Perceived complexity and relative advantage of the intervention*	x					x	
*Perceived successful strategies with implementers & patients*	x					x	
*Perceived roles of intervention champions & opinion leaders*	x					x	
*Facilitators & barriers to implementation*						x	
*Sustained impact of intervention on HIV continuum of care*							x
*Integration into routine practice; reasons for maintenance/discontinuation*							x
Phone Call to Patient about Linkage to HIV Care		x	x	x	x		

^a^Oraquick HIV Testing to be administered prior to study enrollment to adults reporting no prior HIV diagnosis or HIV testing within the prior 12 months

^b^Case Adherence Index Questionnaire to be administered prior to study enrollment and to suspected defaulting participants only

^c^Demographics include includes age, sex, education, religious affiliation, household size, marital status, highest level of education

^d^Visit only occurs if PLWH has not linked to care within 7 days

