All PLWH and TH will meet for scheduled study visits with a member of the study team at enrollment (baseline) and then at 12 and 24 months following enrollment to complete structured surveys. Qualitative interviews will be held throughout the study period, beginning at the time of enrollment. We will invite all intervention arms TH and clinical liaisons, as well as a sample of PLWH, HIV clinicians, and policymakers, to participate in these interviews. Study participants may request to discontinue participation in the study at any time. If a study participant fails to attend their 12-month or 24-month research study visits, they will be considered lost to follow-up. All participant data will be analyzed under the principle of intention-to-treat.

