#### Statistical methods for secondary outcomes

Secondary analyses based on *p* values adjusted for multiple comparisons included fitting regression models to determine the impact of the intervention on linkage to care within 7 days, ART initiation, ART adherence, and retention in care at 12 months. To evaluate ART adherence, we will compare the binary outcomes and continuous values for hair tenofovir concentration between study arms. The effect of the intervention on quality of life will be assessed using mixed effects linear regression by comparing the intervention and control groups. We will also evaluate changes in quality of life measured over 12 months by paired *t*-test. Finally, we will evaluate sex as a biological variable to assess whether the intervention’s effect differs between men and women.

For the implementation evaluation, quantitative analysis will proceed with a descriptive statistical analysis for continuous variables such as the TFA and fidelity scores. Outcomes will be compared across TH and HIV clinician sociodemographic characteristics using logistic regression and mixed linear models. Mixed effects logistic regression models will be used to assess intervention maintenance using HIV viral load in blood plasma samples.

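### The 12-month ART adherence outcome rests only on hair tenofovir, but nothing limits participants to tenofovir-containing ART, so adherence to a tenofovir-free regimen is scored as non-adherence

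*Protocol article*

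**What the plan says.** The section on effectiveness outcomes lists ART adherence at 12 months as a secondary outcome, "defined as a binary outcome of hair tenofovir concentration (> 0.023 ng/mg, reflecting four or more ART doses per week". Table 2 repeats the threshold as the whole outcome definition: "Hair tenofovir concentration of > 0.023 ng/mg". The section on statistical methods for secondary outcomes adds that "we will compare the binary outcomes and continuous values for hair tenofovir concentration between study arms". None of the three places attaches a condition on regimen.

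On who is measured, the inclusion criteria for PLWH do not mention regimen, and the eligibility section closes with "There are no specific exclusions". Previously diagnosed people who report being out of care can enrol. Under the procedures for both study arms, eligible participants are referred to one of five government clinics, where "they can receive free HIV care according to Ugandan MoH guidelines". The article names no regimen.

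No second adherence outcome is set for 12 months. The only other adherence instrument is a screening tool; a footnote to Table 3 reads "Case Adherence Index Questionnaire to be administered prior to study enrollment and to suspected defaulting participants only". On the analysis population, the participant timeline section states: "All participant data will be analyzed under the principle of intention-to-treat".

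**The concern.** A tenofovir threshold can stand for ART doses only in someone whose ART contains tenofovir. The article makes that substitution for every participant, and nothing in the eligibility criteria or procedures makes the premise hold. Previously diagnosed people may return to a regimen that the trial neither sets nor names.

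The outcome therefore mixes two things: whether doses were taken and which drug was prescribed. A participant could have a suppressed viral load and be scored non-adherent at the same 12-month visit, so the adherence result could disagree with the primary result for reasons unrelated to behaviour. At stake is the reading of one secondary outcome, the one closest to the mechanism by which healer support is meant to work.

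**Working it through.** **No figure to reproduce.** The article states no expected rate, sample size or power for the adherence outcome. The link from 0.023 ng/mg to four doses a week rests on cited sources that are not shown and is taken as given.

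**Inputs.**
- True adherence of 60% (control) and 80% (intervention). This is an assumption, borrowed from the viral suppression rates in the sample size section ("will be 60% in the control arm versus 80% in the intervention arm").
- q, the share of adherent participants on tenofovir-free ART. The document does not give it, so a range is shown.

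**Step 1: equal share in both arms.** Someone with no tenofovir intake in the period that the hair reflects falls below the threshold. Hence scored adherence = true adherence × (1 - q), and scored difference = true difference × (1 - q).

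| q | Control | Intervention | Difference |
|---|---|---|---|
| 0 | 60% | 80% | 20 points |
| 5% | 0.60 × 0.95 = 57% | 0.80 × 0.95 = 76% | 19 |
| 10% | 0.60 × 0.90 = 54% | 0.80 × 0.90 = 72% | 18 |
| 20% | 0.60 × 0.80 = 48% | 0.80 × 0.80 = 64% | 16 |

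The ratio of the two rates stays at 1.333. The odds ratio falls from 2.67 at q = 0 to 1.93 at q = 20%.

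**Step 2: unequal shares.** The sign of the bias depends on which arm has the larger share.
- q = 10% control, 5% intervention: 0.60 × 0.90 = 54% versus 0.80 × 0.95 = 76%, a difference of 22 points (too large).
- q = 5% control, 10% intervention: 0.60 × 0.95 = 57% versus 0.80 × 0.90 = 72%, a difference of 15 points (too small).
- No true effect, 60% in both arms: the same two splits give 0.60 × (0.10 - 0.05) = +3 points and -3 points.

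**Step 3: what leaving out tenofovir-free participants does.** Suppose that the tenofovir-free participants are all adherent, and that everyone else, including people not on ART, stays in the denominator. With true adherence p, the rate is p(1 - q) / (1 - pq).
- q = 5%: 0.57/0.97 = 58.8% versus 0.76/0.96 = 79.2%, a difference of 20.4 points.
- q = 20%: 0.48/0.88 = 54.5% versus 0.64/0.84 = 76.2%, a difference of 21.6 points.
- No true effect, q = 5% control and 10% intervention: 0.57/0.97 = 58.8% versus 0.54/0.94 = 57.4%, a false difference of -1.3 points instead of -3.

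In these examples the evaluable-set analysis comes closer to the truth than the literal rule, but it is not free of bias. The difference is exactly 20 points only if the tenofovir-free share is the same among adherent and non-adherent participants.

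**The case against.** The strongest reply is that the problem may hardly exist in practice. Both arms use the same five clinics under one national guideline. If that guideline puts nearly everyone on tenofovir, q is close to zero and so is the error. The assay may have been chosen for that reason. This stands as a limit on size: the document neither gives the share nor says that it is negligible.

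A second reply is that handling a sample from someone not prescribed the assayed drug belongs in the full protocol or SAP. That would be decisive if the article were merely silent. But it fixes the definition in the text and in Table 2, and that definition misclassifies as it stands. A restriction held in an unseen document would still differ from the published outcome.

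Three stronger readings are tempting, and the documents support none of them.
- A reader might infer bias against the intervention, if healer support brings back more treatment-experienced people whose regimen is then changed. With 5% tenofovir-free in control and 15% in intervention, the scored rates would be 57% versus 0.80 × 0.85 = 68%, only 11 points. Nothing in the article supports such a split or its direction.
- A reader might infer that regimen is not recorded because Table 3 has no row for it. Table 3 lists visit activities, and it has no row for ART (re)initiation either, which is a stated secondary outcome.
- A reader might infer that restricting to tenofovir users settles the matter. Regimen arises after randomization, so the restriction can select differently by arm, and it departs from the intention-to-treat statement. Reporting counts by arm shows that selection but does not remove it.

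**Conclusion.** The point holds as a defect in the definition of a secondary outcome. As written, adherence to tenofovir-free ART is scored as non-adherence and enters the continuous comparison near zero, and no other part of the article corrects this.

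Its size cannot be determined from the document. An equal share q shrinks the true difference by the factor (1 - q): a loss of 1 point in 20 at 5% and 4 points in 20 at 20%. Unequal shares could move the result either way. These figures rest on assumed adherence of 60% versus 80% and on assumed shares; the factor (1 - q) does not depend on the assumed adherence rates. If nearly all participants receive tenofovir, the effect is small, and recording the regimen is how the trial can show it. The primary outcome does not depend on this assay and is unaffected.

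**What to change.** 1. At 12 months, abstract the prescribed ART regimen from the clinic or treatment cards that the study already uses for linkage and retention.
2. In the effectiveness outcomes section and in Table 2, state that the threshold measures adherence only for tenofovir-containing ART.
3. Keep participants who are not on ART in the analysis as non-adherent.
4. Do not score participants prescribed tenofovir-free ART as failures, and do not enter their values in the continuous comparison. Report their number by arm as not evaluable by this assay.
5. Because regimen is a post-randomization variable, also report the all-participant analysis as now defined, plus a sensitivity analysis that classifies the non-evaluable participants in other ways, such as all adherent or all non-adherent. Classifying them all as non-adherent is in effect the present rule, so the all-adherent version is the one that adds information.

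The cost is one extra abstracted field, a sentence in two places, a slightly smaller evaluable set and possible selection by regimen, which item 5 makes visible. The change concerns measurement and analysis only; it does not touch the choice of treatment.
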